## Abstract

**Background:**

Antimicrobial coatings of implants are of interest to reduce infection rate in orthopedic surgery. Demonstration of clinical effectiveness of such coated implants to obtain market approval is challenging. The objective of this article is to define a design for a randomized controlled trial to evaluate the clinical performance of a silver-coating for locking plates for fracture treatment.

**Methods:**

The study design has to respect different criteria, such as feasibility, focus on overall complications, such as functional impairment, fracture healing, and particularly on infection rates. Distal tibia fractures were chosen due to the high prevalence of infections in this type of injuries, which warrants a particular benefit of antimicrobial prophylaxis and thus might allow to see a statistical trend in favor of the coated product. The study design was defined as a randomized, controlled, subject and observer-blinded, multi-center study in subjects with fractures of the distal tibia with a total of 226 patients. A number of 113 patients are planned for each of the two treatment arms with treatment of the fracture with a silver-coated device (first arm) or with an uncoated device (second arm). Inclusion criteria are closed fractures of the distal tibia according to the Tscherne-Oestern classification or open fractures of the distal tibia according to the Gustilo-Anderson classification in subjects older than 18 years. Primary outcome parameter is the Anticipated Adverse Device Effects (AADE) including all typical complications of this type of injury, such as functional impairment of the affected limb, non-union, and infections based on a non-inferiority study design. Also, silver-typical complications, such as argyria, are included. Secondary parameters are infection rates and fracture healing. Follow-up of patients includes five visits with clinical and X-ray evaluations with a follow-up time of 12 months.

**Discussion:**

Demonstration of clinical effectiveness of antimicrobial coatings of fracture fixation devices remains a challenge. Definition of a prospective randomized pre-market trial design and recruitment of clinical sites for such a study is possible. A confirmative proof of the expected clinical benefit in terms of reduction of device-related infections will be addressed with a prospective post-market clinical follow-up study in a second step due to the large sample size required.

**Trial registration:**

ClinicalTrials.gov NCT05260463. Registered on 02 March 2022.

## Administrative information

Note: the numbers in curly brackets in this protocol refer to SPIRIT checklist item numbers. The order of the items has been modified to group similar items (see http://www.equator-network.org/reporting-guidelines/spirit-2013-statement-defining-standard-protocol-items-for-clinical-trials/).

## Introduction

### Background and rationale {6a}

Implant-related musculoskeletal infections have a severe negative effect on patients’ quality of life [1] and a strong negative financial impact on health care budgets [2, 3]. Therefore, all efforts to reduce infection rates by improvement of prophylactic measures should be undertaken including antimicrobial strategies for implants.

Several alternatives have been developed as implant coatings to prevent biofilm formation: gentamicin, povidone-iodine, or silver [3]. For antibiotic-based technologies, there is a potential risk to enhance the emergence of antibiotic-resistance strains [3]. In contrast, the multilevel antimicrobial mode of silver ensures that resistance cannot be easily acquired by single-point mutations [4]. Silver exhibits significant benefits compared to antibiotics as an implant coating, including the lack of clinically relevant silver resistance of bacteria, the broad antimicrobial activity against almost all types of bacteria and fungi, and its good biocompatibility that has already been published in the context with coatings from orthopedic megaendoprostheses [5–8]. The benefits of silver for implant coatings for orthopedic devices have already been established for silver-coated megaendoprostheses in orthopedic tumor surgery with good biocompatibility [5–7, 9] and significant reduction of infection rates in a case-control study [7].

A surface modification based on a plasma electrolyte oxidation (PEO) process with the release of silver ions and antimicrobial properties for locking plates (*aap* Implantate AG, Berlin, Germany) has recently shown good biocompatibility without negative effects on fracture healing [10]. This technology is intended to use silver as a prophylactic antimicrobial agent to reduce the risk for biofilm formation on the implant surface to improve infection prophylaxis for implant-associated infections in fracture patients.

There is currently no silver-based technology commercially available for the prophylactic use in fracture patients and to the authors’ best knowledge, no study protocol in this context has been published before in the literature.

### Objectives {7}

The primary objective of this study is to evaluate the non-inferiority of the silver-coated implants compared to the uncoated implants. Furthermore, as a secondary objective, the clinical benefit of the silver-coated implants in comparison with the uncoated implants should be demonstrated.

### Trial design {8}

This is a 1:1-randomized, controlled, subject and observer-blinded multi-center non-inferiority trial.

### Eligibility criteria {10}

After giving informed consent, Patients older than 18 years who suffer from fractures of the distal tibia (AO type 43 injuries) will be enrolled in the study. The fractures must be either closed with soft tissue damage of grade 1 or grade 2 according to Tscherne Oestern classification [11, 12] or open with soft tissue damage of type I, type II, type IIIA, and type IIIB fractures according to Gustilo-Anderson classification [13, 14] and must be confirmed with radiographic images. Patients with fibula fractures may also be included but must have a fracture of the distal tibia as described before. For these subjects, the fibula fracture will also be treated with coated or uncoated study devices as randomized.

If the patient has a known allergy to silver or any components of the device or has already an implanted silver-coated device inclusion will not be possible.

### Who will take informed consent? {26a}

Patients coming to the study site will be assessed by the treating orthopedic surgeon for potential participation in the study and will be informed in oral and written form by an investigator about the clinical trial. After consent, the patient will be screened for eligibility to participate based on the abovementioned criteria.

### Additional consent provisions for collection and use of participant data and biological specimens {26b}

No additional consent provisions will be obtained. As part of the informed consent form, the permitted handling of the patients’ data according to the General Data Protection Regulation (GDPR) following EU law and applicable national regulations is explained extensively. No biological specimens will be collected.

## Interventions

### Explanation for the choice of comparators {6b}

The summary description and intended purpose of the investigational device are the same as that of the comparator device. The investigational device differs from the comparator device in that its surface which has been modified by the addition of an antibacterial coating by integrating silver agglomerates using a proprietary Plasma Electrolytic Oxidation (PEO) process. Therefore, the comparator device will allow for the safety and clinical benefit of the modified surface to be assessed.

### Intervention description {11a}

Regardless of whether the patient receives the Investigational Device or the Comparator, the study schedule is identical (see Table 2). Each patient will have seven study-related visits.

#### Screening and enrolment

After the patient gave consent, a preoperative baseline for all collected assessments in connection with the defined endpoints will be done. Attention must be paid to the baseline concentration of silver in the blood, since external factors (i.e., working in a photo development laboratory) can have an influence that could falsify the study results if this is not taken into account.

#### Implantation

On the day of the implantation the patient will be randomized to one of the two treatment groups. No specifications are made by the clinical investigation plan for implantation and subsequent care. This lies in the assessment of the treating physician. The first sample for silver level analysis after implantation must be done 24 h (± 12 h) after wound closure. If a drainage has been applied to the patient, a sample of the wound fluid will be collected 24 h (± 12 h) and 48 h (± 12 h) after wound closure to be able to compare the expected high silver concentration on the local area around the implant to the silver concentration in the blood.

#### Follow-up Visits

At the five follow-up (FU) visits of up to a year the patient will be accompanied in his or her healing process and all assessments for the defined endpoints will be made. The point of study termination is defined as the date of 12-month FU for patients with regular study termination. Following completion of the 12-month FU visit, the subject will be treated according to the standard of care practice of the treating surgeon.

### Criteria for discontinuing or modifying allocated interventions {11b}

At any time and without any reason, patients can withdraw from the clinical trial without consequences. Because of compliance reasons, the investigator can end the patient’s participation. The collected data of patients who did not end the trial per protocol will be part of the Safety Analysis Set.

### Strategies to improve adherence to interventions {11c}

Surgeons will be trained in handling of the implants to avoid any issues with the wrong use of the medical device. The study sites will be closely monitored on-site and remote by a clinical research associate (CRA). The CRA will check the training records of the study team and verify the source data. In the course of the clinical trial, an unblinded CRA will visit the study site for implant accountability, counting the implant packaging, and reviewing the device deliveries.

### Relevant concomitant care permitted or prohibited during the trial {11d}

No concomitant care and interventions are prohibited during the trial.

### Provisions for post-trial care {30}

Following completion of the 12-month FU visit, the subject will be treated according to the standard of care practice of the treating surgeon. The Sponsor will maintain an adequate insurance policy covering damages arising out of the clinical trial. This insurance covers the subjects with respect to the risks involved in this study according to the clinical investigational plan.

### Outcomes {12}

Since this clinical trial should demonstrate the non-inferiority of the silver-coated implants the primary outcome is the comparison of predefined AADEs of patients treated with the investigational product and patients who received the comparator. A list of AADEs was defined based on experiences with the non-coated implants (see Table 1). Other outcomes of interest are:To investigate the proportion of subjects with device-related infections occurring after successful implantation of the study device and end of the 12-month FU and compare the rate between the treatment arms.To investigate fracture healing assessed by local and central reviewer and compare the rate of completely healed subjects between treatment arms.To investigate the number of hospitalizations occurring in the first 12 months post-implantation and the nights spent in hospital and compare the numbers between treatment arms.To investigate the change in American Orthopaedic Foot and Ankle Score (AOFAS) at each FU visit and compare endpoint between the treatment arms.To investigate the change in average pain at rest at each FU visit and compare endpoint between the treatment arms.To investigate the change in the disability rating index at each FU visit and compare endpoint between the treatment arms.To investigate all items assessed in the EQ-5D-5L questionnaire.To investigate the proportion of subjects with full weight bearing at each FU visit and compare this endpoint between the treatment arms.To investigate the change in silver serum levels at each scheduled FU visit and compare endpoint between the treatment arms. The change in silver serum level is defined as the difference between the respective silver level at the respective FU and the silver level at Screening/Enrollment Visit.To investigate the proportion of subjects with Treatment Emergent Adverse Events (TEAEs) during the 12-month FU and compare the rate between treatment arms. A TEAE is considered as any AE observed during the 12-month FU which occurred after the start of the implantation surgery.

**Table 1 Tab1:** List of anticipated adverse device effects

	Incidence proportion
Device-related events	
Implant loosening	
Implant failure (e.g., plate or screw breakage)	3% [15], 5% [16]
Local Argyria^a^	23% [17]
Delayed healing/union	2.5% [18]
Procedure-related events	
Non-union	3.7% [19], 6% [15]
Wound infection	
Superficial infection	17% [15]
Deep infection	19% [20]
Malunion	6% [15], 9.5% [21], 10% [18]
Pain	25% [19], 79% [9], 87% [20]
Hematoma	
Lesion of neurovascular structures	1.1% [9] (neuropraxia)
Post-traumatic arthritis	
Shortening of the fibula	
Compartment syndrome	1.1% [9]
Functional impairment	52% [21], 66% [9]
Amputation	2% [15]
Local discomfort	10% [18]

^a^Argyria was reported in implants different from internal fixator plates and with a different coating technique. Due to the much lower systemic exposure level that can be caused by the investigational device the actual incidence is expected to be considerably lower

### Participant timeline {13}

The participant timeline is shown in Table 2.

**Table 2 Tab2:** Study schedule. Assessment windows will be as follows: screening/enrollment visit (day −21 to day 0), implantation (day 0), 1-week FU visit (7 ± 3 days), 6-week FU (42 ± 7 days), 3-month FU (90 ± 14 days), 6-month FU (182 ± 14 days), 12-month FU (365 ± 30 days)

Investigations	Enrollment	Implantation	1-week	6-week	3-month	6-month	12-month
Informed consent	X						
Randomization		X					
Implantation		X					
Adverse event reporting	X	X	X	X	X	X	X
Local Argyria	X		X	X	X	X	X
Assessment of Infection	X	X	X	X	X	X	X
Blood serum (silver levels)	X	X	X	X	X	X	X
Wound fluid (silver levels)		X					
Radiological assessment (X-ray)	X		X	X	X	X	X
AOFAS score	X		X	X	X	X	X
Questionnaires: VAS (pain), DRI, EQ-5D-5L	X		X	X	X	X	X
Assessment of weight bearing	X		X	X	X	X	X

### Sample size {14}

The sample size calculation is based on the number of expected AADE of uncoated system compared to the coated system. A one-sided test at the 5% significance level and 80% power requires 96 subjects successfully implanted with either system to detect non-inferiority at a margin of 10%, i.e. an overall number of 192 subjects with successfully implanted study devices. Accounting for a 15% drop–out rate due to screening failures and surgical failures a total sample size of 226 screened subjects is considered sufficient to achieve the primary objective of the study.

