## Assignment of interventions: allocation

### Sequence generation {16a}

Treatment allocation to coated or uncoated investigational device will be randomized in 1:1 ratio. With a stratification by site and by severity of the soft tissue lesion [3 groups: (1) closed and Gustilo-Anderson type I open; (2) Gustilo-Anderson type II open; (3) Gustilo-Anderson type III open] [13, 14]^.^

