## Statistical methods

### Statistical methods for primary and secondary outcomes {20a}

All statistical calculations will be made in SAS. A statistical analysis plan will be developed and finalized before data base lock and unmasking describing in detail the planned statistical analysis.

All study endpoints of this study will be summarized using descriptive summary statistics, i.e., arithmetic mean, standard deviation, minimum, median, and maximum for quantitative variables by treatment group. For qualitative variables, absolute and relative frequencies will be reported. For event-based variables (e.g., AEs) the number of events as well as the incidences (i.e., number and percentage of affected subjects) will be provided.

The primary null hypothesis that will be tested is that the difference in proportion of subjects who have at least one predefined AADE (between investigational coated device and comparator (uncoated)) is greater than or equal to 0.1 (i.e., the alternative hypothesis is successfully met if the upper bound of a two-sided 90% CI is less than +0.1).

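### The unqualified 80% power at 96 per arm needs, with equal true rates, a composite AADE rate of at most 8.5% (which Table 1 excludes) or at least 91.5% (where the 10-point margin cannot be exceeded)

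*Protocol article*

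**What the plan says.** The protocol article, Sample size {14}, sets "A one-sided test at the 5% significance level and 80% power" and concludes that "80% power requires 96 subjects successfully implanted with either system to detect non-inferiority at a margin of 10" percent, which makes "an overall number of 192 subjects with successfully implanted study devices". Allowing for 15% losses brings the total to 226. The section says that the calculation rests on the AADEs expected with the two systems, but gives neither a rate nor a difference.

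Statistical methods {20a} defines the primary comparison as the "difference in proportion of subjects who have at least one predefined AADE". Non-inferiority is shown if "the upper bound of a two-sided 90% CI is less than +0.1". This matches the one-sided 5% level. Sequence generation {16a} adds: "Treatment allocation to coated or uncoated investigational device will be randomized in 1:1 ratio".

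Table 1, under Outcomes {12}, lists the AADEs with literature incidences. The largest are pain (25%, 79%, 87%) and functional impairment (52%, 66%). Superficial and deep infection stand at 17% and 19%. No composite rate is given.

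**The concern.** With a fixed absolute margin, the power of a comparison of two proportions depends strongly on the event rate, because the variance p(1-p) is largest near 50%. An endpoint that counts any one of many complications cannot be rarer than its commonest component, and Table 1 puts several components well into the range of high variance. The 80% is stated without a condition, yet it does not obviously fit those rates.

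This is the only power statement for the primary objective. If the composite rate lies in the middle of the scale, a coated plate that is truly equivalent could miss the criterion far more often than the planned one time in five. If the rate is very high, the criterion is easy to meet, but for a reason that says little about the coating.

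**Working it through.** **Inputs.** One-sided alpha 0.05 (z = 1.645), power 80% (z = 0.842), margin 0.10, 96 per arm and 1:1 allocation are stated. Equal true rates in the two arms are my assumption, since the article states no difference.

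**Reproducing the plan's figures.** The inflation is right: 192 / 0.85 = 225.9, so 226. The 96 cannot be reproduced directly because no rate is given, so I solved for the rate that yields it.

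n = (1.645 + 0.842)² × 2p(1-p) / 0.10², with (1.645 + 0.842)² = 6.183.

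Setting n = 96: p(1-p) = 96 × 0.01 / (2 × 6.183) = 0.0776, so p = 0.085 or p = 0.915.

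Power is 80% or more at or below the first value, and at or above the second.

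**Low solution.** The composite is at least as common as functional impairment (52% to 66% in Table 1). The infection rows alone (17%, 19%) already exceed 8.5%.

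**High solution.** At an uncoated rate of 91.5% the coated rate can be at most 100%, a difference of 8.5 points. For any uncoated rate above 90%, a difference of 0.10 or more is impossible. The null hypothesis in {20a} then cannot be true.

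**Between the two.** Power = Φ(0.10 / √(2p(1-p)/96) − 1.645). At p = 0.52, for example, the standard error is 0.0721, 0.10/0.0721 = 1.387, and Φ(−0.258) = 0.398.

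| Composite rate, both arms | Power at 96 per arm | n per arm for 80% |
|---|---|---|
| 52% | 40% | 309 |
| 66% | 43% | 278 |
| 79% | 52% | 206 |
| 82% | 56% | 183 |
| 87% | 66% | 140 |
| 90% | 75% | 112 |
| 91.5% | 80% | 97 |
| 98% | above 99% | 25 |

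Exact binomial enumeration of the 90% Wald interval rule agrees closely: 41.4% at 52%, 42.3% at 66%, 53.2% at 79%, 67.2% at 87%, 75.5% at 90% and 80.6% at 91.5%.

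**Where Table 1 puts the composite.** If the components were independent (an assumption; argyria and the rows without a figure left out), the composite is one minus the product of the event-free proportions.
- Lowest values: 1 − (0.97 × 0.975 × 0.963 × 0.83 × 0.81 × 0.94 × 0.75 × 0.989 × 0.989 × 0.48 × 0.98 × 0.90) = 1 − 0.179 = 82%.
- Highest values: 1 − (0.95 × 0.975 × 0.94 × 0.83 × 0.81 × 0.90 × 0.13 × 0.989 × 0.989 × 0.34 × 0.98 × 0.90) = 1 − 0.020 = 98%.
- With complete overlap, the composite equals its largest component: 52% on the lowest values, 87% on the highest.

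**Dropping equal rates.** The true reduction in the coated arm that restores 80% power at 96 per arm is about 7.9 points at an uncoated rate of 52%, 4.4 at 82% and 2.5 at 87%.

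**The case against.** The strongest reply is that Table 1 does not fix the composite rate. Its rows are incidences from different cited studies, and for an endpoint that counts any one event each row is only a floor. Functional impairment at 66% and pain at 79% come from the same cited source. If independent, they already give 1 − 0.34 × 0.21 = 92.9% and power of about 85%. At the upper values power exceeds 99%.

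That stands. A reader might infer from the 52% and 87% rows that the trial's power is 40% to 66%, or that an equivalent plate would fail about half the time. The documents do not support this, because it treats one component as the whole composite. Taken together, Table 1 is compatible with power from about 40% to above 99%.

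Second, zero difference is my assumption. The Sample size section refers to expected AADEs in both systems, and the Discussion hopes for fewer infections with the coating. A modest assumed advantage could therefore lie behind the 96. That is possible, but the section states none, and its 80% carries no such condition.

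Third, a journal article condenses a fuller plan that may give the rate. So I do not count the missing rate as a fault in itself. However, no equal-rate value in that plan could fit Table 1, yield 80% and leave a margin that can be exceeded.

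Fourth, an easily met margin at high rates is strictly a question about the margin, and the power arithmetic there is correct. I agree. It matters here because that region is the only equal-rate one in which the stated power agrees with Table 1.

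**Conclusion.** The point holds in this form: the unconditional 80% does not follow from the article's own event rates. With equal true rates it needs a composite of at most about 8.5%, which Table 1 contradicts, or at least about 91.5%, where non-inferiority at 10 points is an empty claim. For composite rates from 52% to 90%, power is 40% to 75%. The remaining route, a true coated-arm advantage of roughly 2.5 to 8 points for uncoated rates between 87% and 52%, is not stated.

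The low solution falls whatever the overlap between components, provided that Table 1's incidences broadly carry over to the trial's endpoint. The 82% and 98% rest on independence. The conclusion is not that the trial is shown to be underpowered. It is that the stated power needs a condition, and the condition has to be reconciled with Table 1.

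**What to change.** In Sample size {14}, state the composite rate assumed for the uncoated arm and the assumed coated-minus-uncoated difference behind 96 per arm, and reconcile both with Table 1. Replace the unqualified 80% with the power of 192 evaluable subjects over the whole plausible range: with equal rates, about 40% at 52%, 56% at 82%, 66% at 87%, 80% at 91.5% and above 99% at 98%. Add that above an uncoated rate of 90% the 10-point margin cannot be exceeded. If a coated-arm advantage was assumed, say so and give its size.

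Check the assumed rate against the blinded pooled AADE rate before database lock. The analysis plan is to be finalized before lock and unmasking, so the result can be recorded there.

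The cost is wording in the protocol and analysis plan, one blinded tabulation, and a less favorable power statement over much of the range. No extra patients are asked for, and trial conduct does not change.
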